## Methods/design/interventions

This study is a single-center, prospective, randomized, controlled trial of patients with spine metastasis with two arms. The study protocol has been reported in accordance with the Standard Protocol Items: Recommendations for Clinical Interventional Trials (SPIRIT) guidelines (see Additional file 1). Eligible patients will have spine metastasis from T5 to L5 (within the treatment limits of RFA/PVA). There is no limit to the maximal involvement of contiguous vertebral bodies with metastatic disease, as long as an index lesion of pain can be determined and fewer than two sites would undergo RFA/PVA in total. All patients will undergo an MRI of the involved spine within 6 weeks prior to registration to determine the extent of spine involvement and must score their index lesion-associated pain as at least 5 using the Numerical Rating Pain Scale (NRPS). In the control arm, patients will receive conventional palliative EBRT to any of the following dose and fractionation schedules per the discretion of the treating physician: 20 Gy in 5 fractions, 24 Gy in 6 fractions, and 30 Gy in 10 fractions. Single fraction radiotherapy is not allowed in this study since this has been associated with higher incidence of re-treatment [9] and that fractionated regimens are more traditionally used in patients who have undergone percutaneous or surgical interventions. Patients randomized to the experimental arm will undergo RFA/PVA followed by EBRT using the same dose/fractionation schedules. All supportive therapy for optimal medical care will be given during the study period at the discretion of the attending physician(s) within the parameters of the protocol and documented as concomitant medications. Chemotherapy is not permitted within 24 h prior to or concurrently with EBRT. In addition, the patient can receive chemotherapy no earlier than 24 h after EBRT. If a deviation from the protocol occurs, the PI will complete and electronically submit the “Protocol Deviation Form.”

The target parameters will be measured and recorded at the baseline clinic visit (on the day of treatment) and daily at home with collection of weekly measurements at 1, 2, and 3 weeks after treatment, and at 3, 6, 12, and 24 months following treatment with imaging and QOL assessments (see Table 1). There will be no special criteria for discontinuing or modifying allocated interventions given that both are standard of care interventions (Fig. 1).

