### Assessment of the primary and secondary endpoints

The primary endpoint for this trial is pain response, defined as complete or partial pain relief, as measured using the NRPS at 3 months (post-treatment pain score of 0 or at least 3 NRPS points). The NRPS is a widely utilized assessment of pain intensity in oncologic clinics and has demonstrated reliability in studies of small sample sizes and in settings where repeated measurements are obtained to monitor changes in pain intensity over time [11]. Using this scale, complete pain relief is defined as a pain score of 0 with no increase in narcotic pain medication, and partial pain relief is defined as a reduction in numerical pain score of at least 2 points at the index site with no increase in pain medication.

Secondary pain response endpoints include the rapidity of pain response, as defined as the time from study entry to complete or partial pain relief, and duration of pain response, as defined as the time from complete or partial pain relief to pain worsening (≥ 3 NRPS points). To assess these outcomes, patients will complete the NRPS for each treatment site at the baseline clinic visit (on the day of treatment) and daily at home with weekly measurements at 1, 2, and 3 weeks after randomization in addition to a diary of their pain medication use and any side effects they experience related to the treatment. One month after treatment, patients will complete the NRPS, and at the clinic visit, the research team will consolidate the patients’ pain level scores, pain medications, and document adverse events. Imaging of the treated spine will be obtained at baseline and at 3, 6, 12, and 24 months after randomization to assess the response to treatment as well as subacute or long-term change of the vertebral bone.

The study hypothesis is that given the potential benefit of combined modality treatment in providing rapid and durable pain relief, QOL will improve after RFA/PVA and EBRT. Therefore, a number of QOL outcomes will also be prospectively collected in this study, including QOL, as measured by the Functional Assessment of Cancer Therapy (FACT-G) [12]; patient perception of pain, as measured by the Brief Pain Inventory (BPI) [13]; and health utilities, as measured by the EuroQol (EQ-5D) [14] at 3, 6, 12, and 24 months post-study randomization.

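### Pain response starts at a 2-point fall without more pain medication but ends only at a 3-point worsening with no medication condition, so some relapses go uncounted in duration of response

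*Protocol article*

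**What the plan says.** All the definitions stand in the protocol article, section Assessment of the primary and secondary endpoints.

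- **Start of response, complete:** "complete pain relief is defined as a pain score of 0 with no increase in narcotic pain medication".
- **Start of response, partial:** "partial pain relief is defined as a reduction in numerical pain score of at least 2 points at the index site", again on condition that pain medication does not increase.
- **End of response:** duration is "the time from complete or partial pain relief to pain worsening", with worsening set at 3 or more NRPS points. No medication condition is attached.
- **A competing response threshold:** the primary-endpoint sentence describes response as "post-treatment pain score of 0 or at least 3 NRPS points", which does not agree with the 2-point definition of partial relief.

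On entry, patients "must score their index lesion-associated pain as at least 5 using the Numerical Rating Pain Scale (NRPS") (Methods/design/interventions), with no upper limit given. Pain medication is recorded: home scores are kept "in addition to a diary of their pain medication use", and Table 1 lists medication documentation beside the pain score before treatment and at follow-up.

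Under Statistical analysis, duration of response is analysed by Kaplan-Meier medians, a stratified log-rank test at 0.025 and a Cox model.

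**The concern.** A duration endpoint should end when the patient no longer has what started it. Here entry takes 2 points and stable medication, while exit takes 3 points and ignores medication. Two kinds of patient have lost their response by the entry definition yet still count as responding: the minimal responder who is back at the baseline score, and the responder whose score holds only because analgesics were increased.

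Duration of response is a named secondary objective with its own test and hazard ratio. Relapses that are missed or counted late lengthen the Kaplan-Meier medians. If minimal responders are more common in one arm, the comparison is distorted as well.

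**Working it through.** **The plan's own figure.** The article gives no event count or power for duration, so there is nothing to reproduce for this endpoint. The response rates used in step 5 are the feasibility-study rates in the Background section, 93.3% and 59.9%. They are the rates behind the stated 52 patients. With a pooled rate of (0.599 + 2 × 0.933)/3 = 0.822, the two-proportion formula at two-sided 0.05, 80% power and 2:1 allocation gives

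n(control) = [1.96 × √(0.822 × 0.178 × 1.5) + 0.842 × √(0.599 × 0.401 + 0.933 × 0.067/2)]² / 0.334² ≈ 16.5, rounded up to 17.

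That makes 17 + 34 = 51, against 52 stated.

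**Set-up.** Let b be the baseline score and r the score at partial response. Assume integer scores on a 0-10 scale (the range is not stated in the article). Then b runs from 5 to 10 and r from 1 to b − 2, which gives 3 + 4 + 5 + 6 + 7 + 8 = 33 possible pairs. These are combinations of scores, not proportions of patients.

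**1. Worsening counted from the score at response.** The event needs a score of at least r + 3.
- Return to baseline is a rise of b − r. It is missed when b − r < 3, that is, when relief was exactly 2 points: 5 to 3, 6 to 4, 7 to 5, 8 to 6, 9 to 7 and 10 to 8 (6 of 33 pairs).
- The event is impossible when r + 3 > 10. Only 10 to 8 qualifies (1 of 33).
- Complete responders are unaffected, because a return from 0 to a baseline of 5 or more is a rise of at least 5.

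**2. Worsening counted from baseline.** The event needs at least b + 3.
- Return to baseline is never an event (33 of 33).
- The event is impossible when b + 3 > 10, that is, for baselines 8, 9 and 10 (6 + 7 + 8 = 21 of 33 pairs).

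**3. Medication.** The end-of-response rule contains no medication term, so an analgesic increase at a held score is not an event under either reading. This needs no assumption about the scale or the reference score.

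**4. If the 3-point wording governs response.** The pairs fall to 2 + 3 + 4 + 5 + 6 + 7 = 27. Counted from the score at response, 0 of 27 return to baseline unseen and 0 make the event impossible. The medication gap stays. Counted from baseline, 27 of 27 still return without an event.

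**5. Possible imbalance between arms.** Assume the fall in score is normal with the plan's rates as P(fall ≥ 2) = p. Then P(fall ≥ 3) = Φ(z_p − 1/SD), with z = 1.499 for 0.933 and 0.251 for 0.599. The share of exact 2-point responders among responders is [p − P(fall ≥ 3)]/p.

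| Assumed SD | Experimental | Control |
|---|---|---|
| 1.5 | (0.933 − 0.797)/0.933 = 15% | (0.599 − 0.339)/0.599 = 43% |
| 2.5 | (0.933 − 0.864)/0.933 = 7% | (0.599 − 0.441)/0.599 = 26% |
| 3.5 | (0.933 − 0.887)/0.933 = 5% | (0.599 − 0.486)/0.599 = 19% |

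The control share is the larger at each SD, but the figures move by a factor of two to three.

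**The case against.** **The article condenses a fuller protocol.** The missing reference score may well be settled in the full protocol or analysis plan, and its absence here is no finding. That stands. What remains is what the article does state: 2 points with a medication condition to enter, 3 points without one to leave. Naming a reference score would not remove that mismatch.

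**The 2-point start is itself in dispute.** The primary-endpoint sentence says 3 points. If that governs and worsening is counted from the score at response, the score part disappears (step 4). This stands as a condition on the finding. However, duration starts from partial relief, which the article expressly defines as 2 points, and the medication gap survives either way.

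**A larger exit threshold can be deliberate.** It guards against fluctuating scores being read as relapse. That is a fair reason not to end response at a single reading just below the threshold: with daily home scores, 7 to 5 to 6 on one day should not count. It does not justify keeping a patient who is fully back at baseline in response.

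**Stronger readings the documents do not support.**
- A reader might infer that the 7 to 5 to 7 patient can never fail. On the response-score reading that patient has an event on reaching 8; the event is missed or delayed, not impossible.
- A reader might infer that half the eligible entry scores (8, 9 and 10 out of 5 to 10) can never produce an event. That requires counting from baseline, the less natural reading of a period running from relief to worsening, and also an unstated 0-10 scale.
- A reader might take 7% against 26% as the size of the problem. Those shares rest on one SD that the article does not give. The model also describes change at a single time point, whereas duration starts at first relief, and at SD 2.5 it puts the mean experimental fall at 5.75 points, more than a patient entering at 5 can have.

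**Conclusion.** The point holds in a limited form. As written, the end-of-response rule does not mirror the start. On the natural reading, exact 2-point responders can lose all their relief uncounted, and under every reading an analgesic increase goes uncounted. Duration of response is overstated. Under the response-score reading the missed relapses may fall more heavily on the control arm, which would work against showing longer durability in the experimental arm.

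The size cannot be fixed from the article. The 5-15% and 19-43% shares are illustrative and depend on an assumed normal change and SD. The impossible-event cases depend on an assumed 0-10 scale, and on the natural reading they reduce to 10 to 8. The score part also depends on the 2-point definition governing response. Only the medication part is free of these assumptions.

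This is one secondary endpoint. It should be corrected, but it does not touch the primary endpoint or the sample size of 52.

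**What to change.** 1. Reconcile the 2-point and 3-point response thresholds in the endpoint section and use one value throughout.
2. Define loss of response as a worsening by that same threshold, counted from the score at response (or from the best score reached), or an increase in pain medication as defined for response. With a common threshold t, a responder has b − r ≥ t, so a full return to baseline always counts; and since r ≤ b − t ≤ 10 − t, the event is always reachable on a 0-10 scale.
3. Apply the rule to the weekly and clinic-visit assessments, or require confirmation at a following assessment, so that one day's fluctuation does not end response.

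Cost: wording in the protocol and analysis plan only, since pain scores and medication are already collected. Reported durations will be shorter. If the 2-point value is kept, a patient with large relief can also reach the event while still well below baseline (9 to 3 to 5 is a 2-point rise with 4 points of relief left). The present 3-point rule has the same feature (9 to 3 to 6), but the lower threshold makes it more frequent, so it should be accepted knowingly.

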### Radiotherapy

All patients enrolled onto this clinical trial will receive EBRT (Fig. 1). CT simulation will be performed after randomization in a stable and comfortable position to allow for reproducibility from simulation to treatment. A variety of immobilization systems may be utilized, depending on the location and extent of spine disease to be treated. Image co-registration of the diagnostic MRI to the simulation CT can be performed if there is concern for soft tissue tumor component or epidural extension of disease. The gross tumor volume (GTV) contour represents the index spine lesion(s) and should include the entirety of the vertebral body, canal, pedicles, transverse processes, and spinous process as well as any paraspinal or epidural disease, if present. The clinical target volume (CTV) will include the involved index spine lesion(s) as well at least one spine level superior and inferior to the index lesion(s). Depending on site, treatment technique, and immobilization, the planning target volume (PTV) will consist of a 3–5-mm circumferential expansion only. Patients may be treated with 3D-CRT or IMRT at the discretion of the treating physician. The following fractionation schedules will be deemed equivalent and used in this study: 20 Gy in 5 fractions, 24 Gy in 6 fractions, and 30 Gy in 10 fractions [15].

### Radiofrequency ablation and vertebral augmentation

Patients randomized to RFA/PVA will undergo the procedure under moderate sedation in the angiographic suite or with monitored anesthesia care in the operating room. RFA/PVA will be performed with the patient in the prone position. Unipedicular or bipedicular approaches will be used depending on the anatomy and location of the metastatic spine disease. During the procedure, 10-G trocar needles will be placed via a transpedicular or parapedicular approach, and once positioned, RFA will be performed. All RFA procedures will be performed with the OsteoCool™ RF Ablation System (Medtronic Inc.) through the trocar needles. This consists of a coaxial, bipolar technology which delivers RF energy to the site of spine disease. The internally cooled ablation probes control the temperature which helps to keep RF heating within the desired treatment area and reduces the potential thermal damage to the adjacent tissue. Two probes may be used simultaneously, depending on the anatomy, to achieve larger ablation zones, and time adjustments can be made to control the size of the ablation zone. Once the RFA procedure has completed, PVA will be performed, as necessary, using 11-G needles advanced through the trocars and into the anterior 1/3 of the vertebral body. Kyphon high viscosity bone cement will be administered until the cement adequately fills the vertebral body/ablation zone or until the cement leakage precludes additional filling of the vertebral body. Kyphoplasty balloon augmentation will be performed at the discretion of the operator prior to cement administration. Once the entire procedure is completed, the patient will be transferred to the recovery area for a minimum of 3 h to allow the bone cement to solidify. Patients will be discharged the same or next day.

### Data management

MCI provides an in-house Clinical Scientific Review Committee (CSRC). The CSRC is responsible for reviewing all diagnostic, therapeutic, and non-therapeutic cancer research studies conducted at MCI. The MCI Data Safety and Monitoring Committee (DSMC) is responsible for assessing study progress, the reporting of adverse events and unanticipated problems, and the accuracy and integrity of the research data and protocol compliance. The DSMC is composed of representative physician experts and meets requirements as set forth from the NIH. This study will be reviewed by the MCI DSMC, independent from the investigator and study funder, every 3 months as per the assigned risk score. Both committees collaborate to ensure that the clinical trial is being conducted in regulatory compliance.

MCI studies are each assigned one or more Clinical Research Coordinators (CRCs) and Research Assistants (RAs) based on therapeutic area. CRCs are responsible to assist the PIs in the scheduling of patients and collection of study-related data from patients (surveys/questionnaires). RAs are responsible for data entry into MCI’s electronic data capture (EDC) system. MCI Data Management Coordinators (DMCs) are responsible for creating electronic Case Report Forms (eCRFs) for research study. RAs enter data into these eCRFs, which is then validated. At interim and/or final analysis, MCI DMCs export the study dataset and provide it to the PI and MCI Biostatistician for data analysis.

Data will be entered into MCI’s electronic data capture (EDC) system (21 CFR Part 11 compliant), which is a secured system used to collect and manage data for clinical research studies. This system is currently in use for MCI institutional studies. Patients will be identified by initials only (first, middle, last); if there is no middle initial, a hyphen will be used (first-last). Last names with apostrophes will be identified by the first letter of the last name. Data collected during the course of research will be kept strictly confidential and only accessed by members of the study team. Other staff employed by BHSF (sponsor) may have access to study participant data as part of their routine job duties. All staff are governed by the BHSF confidentiality policy and HIPAA guidelines.

### Statistical analysis

Based on the reported incidence of complete or partial pain response from the results of the feasibility matched cohort study of RFA/PVA and EBRT [8], with a two-sided *α* = 0.05 and *β* = 0.20 and a study design of 2:1 randomization scheme (RT plus PVA/RFA:RT), the study will be adequately powered with 52 patients (35 in the RT plus PVA/RFA arm and 17 in the RT arm). Assuming a 5% ineligibility rate, a death rate of 15%, and a patient non-compliance rate of 15%, the total sample size required would be 80 patients. No interim analyses with treatment efficacy results are planned. The primary endpoint is complete or partial pain response at 3 months after randomization, and all eligible, randomized patients will be included in the analysis regardless of treatment compliance (intent-to-treat analysis). Descriptive statistics of the actual change scores, mean change scores, and standard deviations will also be reported. For analysis of the secondary pain response endpoints (rapidity of pain response and duration of pain response), the median time to each outcome variable will be estimated using the Kaplan-Meier approach, the stratified log-rank test will be used to test for statistically significant differences with an α = 0.025, and the Cox proportional hazards regression model will be used to determine hazard ratios and 95% confidence intervals for the treatment differences. Moreover, unadjusted ratios and adjusted ratios for radiosensitive vs. radioresistant histology will be computed. The incidence of adverse events will be reported according to CTCAE v5.0, and differences in the rates at 3 months between the two treatment arms will be tested using the two-sided chi-square test at the 0.05 significance level. To analyze differences in QOL, global pain, and health utility, changes in FACT-G, BPI, and EQ-5D will be described with longitudinal data analysis. The mean differences will be compared across the treatment arms using the two sample *t* test at the 0.025 significance level. The relationship between treatment response and QOL will also be analyzed using the two sample *t* test at the 0.025 significance level.

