Radiofrequency ablation, with or without percutaneous vertebral augmentation (RFA/PVA), has been used to treat pathologic fractures associated with spine metastasis with high rates of initial pain response [6]. Using this technique, disease in the central portion of the vertebral body, or that approaching the posterior elements, is first treated with lethal thermal radiofrequency (RF) energy, and the remaining bone is reinforced with cement to provide stability. Retrospective series have demonstrated significant early pain response and reduction in narcotic use as early as 1 week post-treatment [7]. Investigation into the benefits of a multi-modality approach is warranted, as RFA offers rapid pain relief but has limited oncologic effect by not addressing the entirety of the vertebral metastatic disease, especially in lesions in paraspinal locations and with disease in posterior elements. A small, non-randomized feasibility study of RFA and EBRT forms the basis of the combined modality approach investigated in this trial. In this study of 15 patients with bone metastasis and a pre-treatment pain score of at least 5 treated with RFA and EBRT (20 Gy in 5 fractions) matched to patients treated with EBRT alone, higher rates of complete pain response (53.3 vs. 16.6%, *p* = 0.027) and overall pain response (93.3 vs. 59.9%, *p* = 0.048) were observed [8]. This study was limited by the RF technology available at the time, lack of PVA in at-risk patients, as well as small sample size; therefore, further randomized prospective evidence is needed to characterize the benefits of modern combined modality techniques.

The primary objective of this randomized, controlled trial is to determine whether RFA/PVA in addition to EBRT improves pain control compared to EBRT alone for patients with spine metastasis. Secondary objectives include determining whether combined modality treatment improves the rapidity of pain response, duration of pain response, patient reported pain impact, health utility, and overall quality of life (QOL).

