**Table 1 Tab1:** Study parameter table

Assessments	Pre-treatment	1 month from randomization	Follow-up: At 3, 6, 12, 24 months from randomization
History/physical	Within 2 weeks prior to registration		X
Performance status	Baseline		X
Neurological exam	Within 1 week prior to registration		X
Imaging of the spine (CT scan/bone scan is allowed, MRI preferred)	Within 6 weeks prior to registration		X
Numerical rating pain scale and documentation of patient’s pain medication^a^	Within 1 week prior to registration	(On the day of treatment) (At home: Daily with cumulative weekly measurements at 1, 2, and 3 weeks; bring to clinic at 1 month) In clinic at 1 month	X
FACT-G (FA), BPI (QL), EQ-5D (HP)	Baseline		At 3, 6, 12, and 24 months from randomization
Adverse event evaluation		X	X

^a^NRPS at 3 months is required for analysis of the primary endpoint

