Patients enrolled onto this trial will be stratified according to the tumor type (radioresistant [soft tissue sarcoma, melanoma, and renal cell carcinoma] versus other non-hematologic tumor histologies). The treatment allocation scheme will be used for randomization to balances these patient factors [10]. Within each stratum, patients will be randomized in a 2:1 ratio to either RFA/PVA and EBRT or EBRT alone. This unequal randomization was chosen given the well-known and documented pain response rates to EBRT, accommodates increased demand for combined modality treatment, allows for a larger sample in the combined modality group to evaluate for potential adverse events, and follows the paradigm established by RTOG 0631. The randomization will be performed by a statistician using stratified permuted block randomization. Allocation concealment technique will be used to prevent selection bias and will be performed on an offsite computer. The recruitment phase will conclude when 52 patients have enrolled in the trial (35 in the RFA/PVA and EBRT arm and 17 in the EBRT alone arm), and it is expected that accrual should be completed over a course of 18 months.

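### The 80% power is calculated for about 52 evaluable patients, but the stated primary analysis keeps all eligible randomized patients, for whom power is roughly 49% to 71% if deaths count as non-response

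*Protocol article*

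**What the plan says.** All of the following is in the protocol article.

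- **Power basis (Statistical analysis).** The design is set "with a two-sided *α* = 0.05 and *β* = 0.20 and a study design of 2:1 randomization scheme (RT plus PVA/RFA:RT", with rates taken as follows: "Based on the reported incidence of complete or partial pain response from the results of the feasibility matched cohort study of RFA/PVA and EBRT". Background gives those rates: "overall pain response (93.3 vs. 59.9%, *p* = 0.048) were observed". The result is that "the study will be adequately powered with 52 patients (35 in the RT plus PVA/RFA arm and 17 in the RT arm".
- **Inflation (same section).** The total becomes 80, "Assuming a 5% ineligibility rate, a death rate of 15%, and a patient non-compliance rate of 15" per cent.
- **Analysis set (same section).** For the primary endpoint, "all eligible, randomized patients will be included in the analysis regardless of treatment compliance (intent-to-treat analysis".
- **Table 1, footnote a (Methods/design/interventions).** "NRPS at 3 months is required for analysis of the primary endpoint".
- **Recruitment and randomization.** Allocation is 2:1, and recruitment ends once 52 patients are enrolled, not 80.

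The article does not say how a patient who dies before 3 months, or who has no 3-month score, enters the primary comparison.

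**The concern.** Inflating a sample size for losses makes sense only for patients who will not be in the analysis. The Statistical analysis section inflates for deaths and non-compliance, then says that non-compliance does not remove anyone and that every eligible randomized patient is analysed. The two statements describe different analysis sets.

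If the intent-to-treat sentence governs, the 15% who die and the 15% who do not comply stay in the denominator. The response rates in the comparison are then not 93.3% and 59.9%, and the stated β of 0.20 no longer applies. If the evaluable-patient reading governs, 30% of patients leave the primary comparison for reasons plausibly related to outcome, and the comparison should not carry the intent-to-treat name. The choice decides who enters the primary analysis, so it has to be fixed before outcome data are examined.

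**Working it through.** **Inputs.** Response 93.3% (combined) and 59.9% (EBRT), from Background. Two-sided α = 0.05, power 80%, 2:1 allocation, 52 patients (35:17), losses of 5%, 15% and 15%, and a total of 80, all from Statistical analysis.

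**Formula.** Two-proportion test with pooled variance under the null and no continuity correction:

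power = Φ{ [ |p2 − p1| − 1.96·√( p̄(1 − p̄)(1/n1 + 1/n2) ) ] / √( p1(1 − p1)/n1 + p2(1 − p2)/n2 ) }

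**Step 1: the plan's 52.** Solving for 80% power gives 17 + 34 = 51, against 52 stated. At 17 and 35, p̄ = 0.824, the null standard error is 0.1126 and the alternative standard error is 0.1262. Then (0.334 − 1.96 × 0.1126)/0.1262 = 0.90, so power is 81.5%. The figure reproduces.

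**Step 2: the plan's 80.** 52/(1 − 0.05 − 0.15 − 0.15) = 52/0.65 = 80 exactly. Other routes miss: 52/(0.95 × 0.85 × 0.85) = 75.8, and 52 × 1.35 = 70.2. So 80 arises by subtracting all three groups in full and analysing the 52 who are left at undiluted rates.

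**Step 3: power for the stated set.** Eligible patients: 80 × 0.95 = 76, about 51:25. The 15% loss rates are applied to these patients, equally in both arms, and deaths count as non-responders.

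| Non-compliers | Combined | EBRT | Power |
|---|---|---|---|
| Keep full benefit | 0.85 × 93.3 = 79.3% | 0.85 × 59.9 = 50.9% | 71% |
| Combined-arm non-compliers respond at the EBRT rate | 0.70 × 93.3 + 0.15 × 59.9 = 74.3% | 50.9% | 53% |
| All count as non-responders | 0.70 × 93.3 = 65.3% | 0.70 × 59.9 = 41.9% | 49% |

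Keeping all 80 (53:27) raises the first and last rows only to 74% and 52%.

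**Step 4: deaths excluded, non-compliers kept.** About 64 patients (43:21), EBRT rate 59.9%.

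- Full benefit retained: 93.3%, power 88%.
- Combined-arm non-compliers at the EBRT rate, as 15% of survivors: 0.85 × 93.3 + 0.15 × 59.9 = 88.3%, power 73%.
- The same, but as 15% of eligible patients (0.15/0.85 = 17.6% of survivors): 0.824 × 93.3 + 0.176 × 59.9 = 87.4%, power 69%.

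The range is about 70% to 88%.

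**Step 5: patients needed for 80% power in the three cases of Step 3.** 96, 147 and 159 eligible. Dividing by 0.95 gives about 102, 155 and 168 randomized.

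**Step 6: if recruitment does stop at 52.** 52 × 0.65 = 33.8, about 34 evaluable (23:11), and power is 65% even at the undiluted rates.

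**The case against.** **Non-compliance may mean something else.** The inflation speaks of patient non-compliance and the analysis rule of treatment compliance. If the former means failing to return the 3-month score, inflating for it does not directly contradict analysing patients whatever treatment they received. That reading is fair. But those patients are still eligible and randomized, so the analysis sentence still includes them. The deaths stand apart from this ambiguity: counted as failures, they alone bring power to 71%.

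**The rule may be in a document not shown.** A condensed article commonly leaves the handling of deaths and missing scores to the full protocol or analysis plan. The absence of the rule is therefore not the complaint. The complaint is that the published total assumes exclusion while the published analysis set assumes inclusion.

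**The two outcomes are not the only ones.** A reader might infer that the trial must either abandon intent-to-treat or lose power. That is too strong. Imputing missing and post-death outcomes at the undiluted rates could keep power near 80%, and excluding deaths while non-compliers keep full benefit gives 88%. The article states no such imputation, and the second set is not all eligible randomized patients.

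**The footnote.** A reader might take footnote a of Table 1 as proof that patients without a score are excluded. It sits on the pain-scale row of a visit schedule and can simply mark a mandatory assessment. The contradiction does not depend on it.

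**Ineligible patients.** A reader might also infer that removing them is a further breach, or that it favours one arm. The documents do not support this. The stated set is limited to eligible patients, which agrees with the 5% allowance. Recruitment and randomization describes review with the procedural teams as part of enrolment, and Inclusion criteria makes treatability with RFA/PVA a condition for everyone.

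**Conclusion.** The point holds as a contradiction within the Statistical analysis section: the 80% power belongs to about 52 evaluable patients at 93.3% and 59.9%, while the declared primary analysis keeps every eligible randomized patient.

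The size depends on how losses are counted. With deaths as non-responders among 76 eligible patients, power is 49% to 71%. With deaths excluded and non-compliers kept, it is about 70% to 88%, on a set the article does not declare. These figures assume that 80 are randomized, that the plan's loss rates apply equally in both arms, and that the feasibility rates are true. Counting deaths as failures is an analysis choice that the article does not make.

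Two stronger conclusions are not warranted. A reader might say that the trial has only about 50% power. That is the worst case, in which every non-complier counts as a failure; a treatment non-complier with a 3-month score would be counted by that score. A reader might also attach a type I error rate to the evaluable-patient analysis. Any such figure needs an assumed pattern of missing data in each arm, and the article gives none.

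**What to change.** In Statistical analysis:

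1. Keep the eligible randomized set as primary, with each patient in the assigned arm.
2. State that death before 3 months, or no 3-month score, counts as non-response, and that a treatment non-complier with a score is counted by that score.
3. Make the evaluable-patient analysis a sensitivity analysis.
4. Restate power under this rule as a range: about 49% to 71% at 76 eligible, using the plan's own loss rates.

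If the evaluable-patient analysis is to stay primary, remove the intent-to-treat label instead. Word footnote a of Table 1 to match whichever choice is made. Reconcile the total of 80 with Recruitment and randomization, which ends recruitment at 52.

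The changes are to wording and need no new procedures. The price is a less favourable stated power. Restoring 80% under the rule would take more patients, as Step 5 shows, and whether to seek them is a separate decision for the sponsor.
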